#### Plans to give access to the full protocol, participant-level data, and statistical code

Since this is experimental data, it will later be published and shared in an aggregated form that cannot be traced back to the individual participant with the national and international scientific community.

### Supervision and monitoring

#### Composition of the coordination center and steering committee for the trial

Researchers involved in the study will be responsible for enrollment, data collection, and treatment of patients. The research team is involved by a senior researcher and will plan monitoring meetings as needed.

#### Data monitoring committee composition, role, and reporting structure

A data monitoring committee was not considered relevant. The rehabilitation treatments that will be compared are feasible for patients and consist mainly of standardized exercise and robotic rehabilitation for balance improvement.

#### Harms

Given the nature of the rehabilitation interventions under study, no harm is expected.

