## Background and rationale

Stroke represents the second leading cause of disability worldwide; its incidence increases with age and around 25% of stroke affected people over 65 years old [1]. Stroke consequences, especially in older adults, affected one or more activities of daily living [2] and largely affect the quality of life and independence of the person and of his/her family. Moreover, stoke outcomes imply large direct and indirect social costs [3].

Motor recovery is essential in patients with stoke outcome [4, 5]; especially in older adults, a recovery of smoother, safer, and more correct walking is an essential requirement to allow the patient to be autonomous in the activities of daily living; trunk control and lower limb motor control are an essential outcome in stroke rehabilitation to prevent falls [6–8]. This is particularly important in this fragile population characterized by multimorbidity, polymedication, and nutritional deficit [9–11]. Several studies and a recent meta-analysis have shown how robotic training associated with physical therapy has influenced functional and motor gait and cognitive outcome after stroke, improving endurance and walking strategies [12–15]. In addition, frequently, stroke causes an impairment of the cognitive function that could affect the deterioration of balance and gait during dual-task activities; the study of these processes can be of interest for rehabilitation purposes [16–20]. Also important in rehabilitation are the motor and cognitive substrates that characterize each patient, which can positively influence the recovery process [21–23].

Considering data of the previous study and patients’ needs in the control of walking and balance, we have hypothesized a robotic-assisted balance treatment associated with physical therapy may be more effective than usual therapy performed by a physical therapist. Therefore, the present study aims to evaluate the effects of technological rehabilitation utilizing a robotic balance platform in terms of improvement in static, dynamic balance, and ambulation (assessed with clinical scales and instrumental measures) on fatigue and cognitive performance (attention, dual-task cost and cognitive-motor interference and on quality of life).

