### Eligibility criteria

Elderly patients (age > 65 years) with ischemic or hemorrhagic stroke outcomes documented through neuroimaging techniques (magnetic resonance imaging or computed tomography) that occurred between 1 and 6 months previously will be included in the study, who have sufficient cognitive abilities to execute simple orders and to understand the physical therapist’s instructions as assessed through the Token Test (score ≥ 26. 5), who are able to walk independently or with minimal assistance, and who are able to understand and sign informed consent.

Patients with systemic, neurological, or cardiac pathologies that make ambulation risky or cause motor deficits, orthopedic or postural problems, plantar ulcers, and partial or total amputation of foot segments will be excluded.

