#### Intervention group

HuG patients will undergo robotic treatment for the improvement of balance through the robotic platform (Hunova® Movendo Technology srl, Genova, IT), 3 times per week, each lasting 45 min, in addition to the conventional treatment. In particular, the technological rehabilitation performed employing a footboard will be mostly aimed at improving the balance both in sitting and standing positions and will be proposed static and dynamic exercises, dual-task exercises, and exercises to improve trunk control.

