#### Criteria for discontinuation or modification of assigned interventions

The physical therapists involved in the study will modulate rehabilitation activities according to the patient’s individual tolerance. This tailoring of treatment will be done to avoid problems arising from pain or fatigue.

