#### Plans to promote participant retention and complete follow-up

In this study, there is no follow-up period after the end of the treatment period. In case participants discontinue the study, only data on the reason for discontinuation will be kept.

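### The Harms section gives an expectation in place of a recording plan, so falls, pain and most other adverse events have no planned route into the data by arm

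*Protocol article*

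**What the plan says.** The Harms section of the protocol article reads in full: "Given the nature of the rehabilitation interventions under study, no harm is expected". It does not define an adverse event, or say who would record one, when, or how events would be summarised.

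Other parts of the article bear on the point:

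- Eligibility criteria: "Elderly patients (age > 65 years) with ischemic or hemorrhagic stroke outcomes documented through neuroimaging techniques", with the stroke 1 to 6 months earlier, and "who are able to walk independently or with minimal assistance".
- Intervention group: patients on the platform (HuG), sitting and standing, "will be proposed static and dynamic exercises, dual-task exercises, and exercises to improve trunk control". These sessions come on top of conventional treatment.
- Background and rationale: "trunk control and lower limb motor control are an essential outcome in stroke rehabilitation to prevent falls".
- Criteria for discontinuation or modification of assigned interventions: therapists adapt activity to tolerance, and "This tailoring of treatment will be done to avoid problems arising from pain or fatigue".
- Plans to promote participant retention and complete follow-up: when a patient discontinues, "only data on the reason for discontinuation will be kept".
- Data monitoring committee: "A data monitoring committee was not considered relevant".

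**The concern.** A harms section should say what will be recorded. This one says what the investigators believe will happen. The experimental arm adds robotic balance work, three times a week for four weeks, to the care that both arms receive. Any extra risk would therefore fall mainly on that arm. The patients are over 65, recently post-stroke, and some need help to walk.

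The trial is preliminary. The Sample size section says that the platform's usefulness in this subgroup has not been studied, and the Discussion says that four weeks is enough to judge feasibility. Tolerability by arm is one of the things such a trial should be able to report. If events are not collected to a plan, a report that no harm occurred would restate the expectation and could be mistaken for a finding.

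**Working it through.** **Step 1. Is there a route for harms elsewhere in the article?** Each place that could hold one was read.

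| Section | Falls, pain or adverse events? |
|---|---|
| Assessment (clinical and instrumental) | No. MFIS and FSMC measure fatigue, as outcome scales. |
| Primary outcome | No (Berg Balance Scale only) |
| Secondary outcomes | No |
| Table 2, study plan | No row |
| Plans for assessment and collection of outcomes | Start and end of the four weeks only, with no collection point during the sessions |
| Statistical methods for primary and secondary outcomes | No safety summary |
| Methods for additional analysis | None planned |
| Strategies to improve adherence | Adherence is monitored in both arms; events are not mentioned |
| Verification of the conduct of the study | Daily and at the end of the four weeks; safety is not mentioned |
| Retention and follow-up | Only the reason for discontinuation is kept |

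Two partial routes exist: discontinuation reasons, and change in fatigue between T0 and T1. A fall, pain, or any other event in a patient who completes the four weeks has neither.

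**Step 2. Arm size.** The Sample size section gives 24 patients in two equal groups, so 24 / 2 = 12 per arm. No figure in the plan is in dispute.

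**Step 3. Would there be anything to record?** The article gives no event risk, so a range of per-patient risks p over the treatment period is assumed. The chance of at least one patient with an event among n patients is 1 − (1 − p)^n.

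| Assumed p | n = 12 (one arm) | n = 24 (whole trial) |
|---|---|---|
| 5% | 1 − 0.95^12 = 46% | 71% |
| 10% | 1 − 0.90^12 = 72% | 92% |
| 20% | 1 − 0.80^12 = 93% | 99.5% |

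Across this range, at least one event in the trial is more likely than not.

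**Step 4. What would full recording show?** With 0 events in n patients, the exact one-sided 95% upper limit is 1 − 0.05^(1/n).

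- One arm: 1 − 0.05^(1/12) = 22.1%.
- Both arms together: 1 − 0.05^(1/24) = 11.7%.
- Upper end of a two-sided 95% Clopper-Pearson interval for 0 of 12: 1 − 0.025^(1/12) = 26.5%.

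The information is limited, but it is an honest bound. Without systematic recording, a zero count has no defined meaning and no bound can be given.

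**The case against.** The strongest reply is that this is a condensed article. The Trial status section cites a protocol version 2, and the Data Availability section says that the protocol can be requested. Event definitions, forms and reporting duties commonly sit in that fuller document or in institutional rules. This stands in part: the article does not say that events will go unrecorded, and nobody can conclude from it that they will. It does not remove the point. The article has a section on harms and fills it with an assumption, so harms are addressed, and addressed badly.

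Three stronger readings are tempting, and the documents do not support them.

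- A reader might infer that the trial will produce no harms information at all. Discontinuation reasons are kept, so a withdrawal caused by harm could show up, and worsening fatigue in either arm would show on MFIS or FSMC.
- A reader might see a contradiction between expecting no harm and foreseeing pain or fatigue. Adapting activity to tolerance is preventive and is compatible with that expectation. Likewise, the Discussion's remark that patients who cannot stand safely are not treated describes a restriction that lowers risk.
- A reader might count the absence of a monitoring committee as part of the defect. With 24 patients, four weeks of treatment and no interim analysis, that is an ordinary choice, and it says nothing about whether events are recorded.

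It can also be said that 12 patients per arm can establish little about safety. That is true, and it is why any summary should be descriptive. It is not a reason to leave out the recording.

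**Conclusion.** The point holds in this form: the article states no plan for systematic recording of falls, pain or other adverse events by arm. What it does keep covers only fatigue scores at two times and the reasons of those who leave. As described, the trial could not support a statement on safety or tolerability by arm.

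The loss is modest in statistical terms. The best case from one arm, 0 of 12, would exclude only a risk above about 22%. The plausibility of events rests on assumed risks of 5% to 20%, because the article gives no rate. The conclusion also assumes that the article reflects what will be collected; a full protocol with an event form would answer it. The primary Berg Balance Scale analysis and the sample size are not affected. The change should be made, but it does not call the main comparison into question.

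**What to change.** Replace the Harms sentence with a recording plan:

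- Record falls, pain and any other adverse event in both arms on one REDCap form.
- Use the same questions on the same fixed schedule in each arm, for example weekly and at T1. Recording at every treatment session would give HuG up to 12 more occasions (3 sessions × 4 weeks), and the counts would then mix harm with unequal ascertainment.
- Note separately any event that occurs during a robotic session.
- Keep these records for patients who discontinue, and amend the retention section accordingly.
- Add a row to Table 2.
- Report the number of patients with an event by arm, with exact confidence intervals and without a significance test.

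The cost is a short form in a system already in use, completed by staff already treating these patients. The article reports enrolment as ongoing and describes an amendment route through the ethics committee. The limitation is that reports will come partly from patients and staff who know the allocation, so the counts are descriptive only.

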#### Frequency and plans for verification of the conduct of the study

Verification will be conducted on a daily basis and at the end of the 4 weeks.

#### Plans for communication of major protocol amendments to relevant parties

Decisions on important changes in the trial, if they are necessary, will be made by the research team and authorized by the ethics committee.

### Dissemination plans

Results will be disseminated through peer-reviewed journals.

## Discussion

The study aims to evaluate the improvement in balance, fatigue, quality of life, and motor and cognitive performance after combined conventional and robotic balance treatment with Hunova® (Movendo Technology srl, Genoa, IT) compared with conventional therapy alone. Treatment efficacy will be defined based on motor outcomes (BBS, MI-LL, TUG, SPPB, AI, WHS, FAC, 10MWT, 6MWT) and cognitive outcomes (FAB, SCWT, SDMT, DCT, TMT) and for disability (BIM), quality of life (EQ-5D), and fatigue (MFIS, FSMC) by performance tests and specific self-administered questionnaires.

A possible limitation of the present study is the “non-early” treatment: in fact, the patient cannot undergo this balance-specific robotic treatment if he/she is unable to stand safely; therefore, the treatment cannot start in the acute phase. The considered period of the rehabilitative treatment, evaluated at 4 weeks (12 sessions), is sufficient to assess the feasibility of the protocol, but follow-up is needed to estimate the retention of maintenance of outcome achievement. Further studies will be conducted to determine these aspects and to evaluate the effectiveness of the treatment in other diseases.

A study on the rehabilitation of the frail population is of particular interest because of the continuing increase in older adults in Western countries. Robotic-assisted assessment to identify the most appropriate and individualized rehabilitation treatment may make it possible to reduce disability and improve the quality of life in this population. This study could allow the identification of tools that are effective for both motor and cognitive improvement to identify new strategies to counter the progression of disability and improve the daily management of elderly patients.

This would reduce direct and indirect social costs, of care and treatment, for the National Health Service and caregivers.

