### Outcome

#### Primary outcome

The primary outcome for motor performance is the BBS value, both in HuG and CoG, at the end of the 4 weeks of treatment.

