### Sample size

Since this is a study of a specific subgroup of patients, on whom the actual utility of the Hunova® has not yet been studied in the literature, it is not necessary to formally estimate a minimum sample size. However, based on Julious’ rules [42], we estimate to enroll a sample of 24 subjects, randomized into two groups of equal size.

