### Statistical methods

#### Statistical methods for primary and secondary outcomes

The sample will be described in its clinical and demographic variables through techniques of descriptive statistics. The normality of the quantitative data will be checked with the Shapiro–Wilk test. Normally distributed quantitative variables will be summarized with the mean and standard deviation (SD) or the median and interquartile range (IQR), otherwise. Qualitative variables will be presented through absolute and percentage frequency tables. The primary objective, i.e., assessment of balance as measured by the increase in values of the BBS between start and end of treatment in the two groups, will be assessed employing an ANCOVA model, where the BBS value at baseline will be shown as a covariate, the BBS at the end of treatment as a dependent variable, and the treatment as a factor. The variations of the different parameters between the two groups at individual time instants will be evaluated, concerning the qualitative variables, by Fisher’s exact test or chi-square test, with Yates correction, where appropriate. Quantitative variables will instead be analyzed utilizing the Student’s *t*-test, in case of normally distributed data, or with the Mann–Whitney *U* test, in the opposite case. The assessment, among secondary endpoints, of fatigue, motor and cognitive performance, quality of life, ambulation quality of life, gait, and balance, and cognitive-motor interference will also be assessed through ANCOVA models, as previously indicated for the primary endpoint. Values of *P* < 0.05 will be considered statistically significant. All analyses will be conducted with R software version 4.1.1. (CRAN ®) and STATA version 16 (STATA Corp).

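### The Discussion defines efficacy on 18 unranked scales, inconsistent with the single BBS primary outcome, and the same unadjusted P < 0.05 applies to all of them

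*Protocol article*

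**What the plan says.** The Primary outcome section of the protocol article reads: "The primary outcome for motor performance is the BBS value, both in HuG and CoG, at the end of the 4 weeks of treatment". The next section lists the other 17 scales as secondary.

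The section on statistical methods for primary and secondary outcomes links the primary objective to BBS, which "will be assessed employing an ANCOVA model, where the BBS value at baseline will be shown as a covariate". Among the secondary endpoints, fatigue, motor and cognitive performance, quality of life, gait, balance and cognitive-motor interference "will also be assessed through ANCOVA models, as previously indicated for the primary endpoint". One threshold closes the section: "Values of *P* < 0.05 will be considered statistically significant". No ranking or multiplicity adjustment goes with it.

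The Discussion then gives the article's only statement of how efficacy is to be defined: "Treatment efficacy will be defined based on motor outcomes (BBS, MI-LL, TUG, SPPB, AI, WHS, FAC, 10MWT, 6MWT) and cognitive outcomes". It goes on with "FAB, SCWT, SDMT, DCT, TMT) and for disability (BIM), quality of life (EQ-5D), and fatigue (MFIS, FSMC". BBS appears there as the first of nine motor scales, with no special standing.

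On size, the Sample size section says: "we estimate to enroll a sample of 24 subjects, randomized into two groups of equal size". It makes no formal sample size estimate.

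**The concern.** A trial with one primary outcome normally draws its efficacy conclusion from that outcome and reads the rest as support. Here the Discussion bases efficacy on the primary outcome and 17 secondary scales together, and nothing says that BBS decides or how a mixed set of results is to be read. The wording of the primary outcome adds to the doubt, because it makes BBS primary for motor performance only. Cognition, disability, quality of life and fatigue all count towards efficacy in the Discussion but have no deciding outcome of their own.

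With 24 patients, 18 scales and one unadjusted threshold, one or more nominally significant scales could turn up by chance. The text as it stands would not stop such a result from being presented as efficacy while BBS showed nothing.

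**Working it through.** **Count of outcomes (Discussion).** Motor 9 (BBS and 8 others) + cognitive 5 + disability 1 + quality of life 1 + fatigue 2 = 18. BBS is one of the 18, so 17 are secondary.

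**Inputs.** The threshold is 0.05 per test, from the statistical methods. Sidedness is not stated, so two-sided is assumed and one-sided is shown as the alternative. There are 12 patients per arm (24 / 2). The correlations between scales are assumptions, because the article gives none. The article states no family-wise error rate, so there is no figure of its own to reproduce.

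**Independent outcomes, no true effect, any one significant scale counted.**
- Either direction: 1 − 0.95^18 = 60.3%.
- Favouring the robot, two-sided tests: 1 − 0.975^18 = 36.6%.
- Favouring the robot, if 0.05 were one-sided: 1 − 0.95^18 = 60.3%.
- Expected number of false positives: 18 × 0.05 = 0.9 in either direction, 18 × 0.025 = 0.45 in favour of the robot.

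**Correlated outcomes.** A simulation drew 18 equally correlated normal outcomes, 12 patients per arm, and applied two-sample t-tests at two-sided 0.05, with 40,000 runs. Its Monte Carlo standard error is at most √(0.5 × 0.5 / 40,000) = 0.25 percentage points.

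| Assumed correlation | At least one, either direction | At least one favouring the robot |
|---|---|---|
| 0 | 59.8% | 36.3% |
| 0.3 | 52.1% | 27.1% |
| 0.5 | 40.8% | 20.6% |
| 0.7 | 29.0% | 14.7% |
| 0.9 | 15.5% | 7.7% |

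The first row agrees with the exact values. With no assumption about dependence, the bounds are 18 × 0.05 = 90% and 18 × 0.025 = 45%.

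**After the change.** If BBS alone decides, there is one test. The error rate is 5% in either direction and 2.5% in favour of the robot (two-sided).

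**What the 18 leave out.** The statistical methods also plan t-tests or Mann–Whitney tests between groups at individual time points. The Assessment section adds posturographic, dual-task, kinematic and kinetic variables that the Secondary outcomes section does not list. These would add tests. In the other direction, the ANCOVA list for secondary endpoints does not name disability, although the P < 0.05 rule is general.

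**The case against.** The strongest reply is that the operative sections do set a hierarchy. BBS is primary, 17 scales are secondary, and the primary objective rests on one ANCOVA. On this view the Discussion sentence only says which instruments are used, in a small pilot with further studies foreseen, and multiplicity among secondary outcomes can be left to an analysis plan that is not shown.

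Part of this stands. The Discussion does not call the 18 scales primary, so inconsistency describes the fault better than outright contradiction. A formal adjustment such as Holm across the secondary scales of a 24-patient pilot is a debatable preference, and the point does not need it. What does not stand is that this is mere missing detail. The sentence is prospective and states what efficacy will rest on, and an analysis plan that made BBS decisive would disagree with it.

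A reader might also infer that the trial has a 60% chance of a false efficacy signal, or will probably find one. The article does not support that, for three reasons:
- It nowhere says that one significant scale is enough.
- The 60% counts results against the robot as well as for it, unless 0.05 is one-sided.
- It requires independence, whereas the Assessment section groups five scales as measures of ambulation and two as measures of fatigue, so positive correlation is likely.

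**Conclusion.** The point holds as an inconsistency in the efficacy criterion: 18 unranked scales in the Discussion against one primary outcome and one primary ANCOVA elsewhere, with a single unadjusted threshold throughout.

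Its size depends on how the 18 results would be combined, which the article leaves open. If any one significant scale counted, the chance under no effect of at least one favouring the robot would be about 37% under independence and about 15% to 27% at correlations of 0.7 to 0.3, against 2.5% for BBS alone. These figures assume two-sided tests. Counting either direction, the figures are about 60% and 29% to 52%. All of them describe what a permissive reading would cost, not the error rate of a rule that the plan states. The inconsistency itself does not depend on them and should be corrected.

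**What to change.** - In the Discussion, state that treatment efficacy is judged on the ANCOVA-adjusted difference in BBS between groups at T1.
- In the statistical methods, state that the other 17 scales and the instrumental gait, posturography and dual-task measures are supportive or exploratory. They would be reported as adjusted differences with 95% CIs and not used as grounds for an efficacy claim.

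No extra patients or data are needed. The sponsor gives up unadjusted efficacy claims on secondary scales. The section on protocol amendments requires ethics committee authorisation for important changes, and this may count as one. The Trial status section reports that enrolment was still ongoing, and no interim analysis is planned, so the wording should be settled before the final comparison between groups.
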